#### Intervention costs

The calculation of out-patient clinic costs will be based on time spent by different personnel categories. Time spent will be recorded according to the three main phases of the treatment procedure: Pre-examination, the IVI-procedure and the post IVI-procedure:Pre-examination services performed by secretaries and nursesIVI-procedure performed by nurse (intervention) or physician (standard care) and time spent by senior consultant on on-call assistance to the nurse or physician respectively.Post-IVI services performed by secretaries.

Number of hours spent will be multiplied by personnel group specific salary levels and adjusted with over-head costs. Data will be recorded on a daily basis using predefined registration forms (Additional file 3). Aggregate costs per patient will be calculated.

Extra educational costs on training nurses will be calculated based on the training program.

#### Other hospital costs

Utilization of hospital services outside the out-patient clinic will be assessed by examining data from the hospital administrative patient register. Costs will be calculated by combining volume of in-patient and out-patient services and their corresponding unit costs.

#### Health care costs outside hospital

Utilization of ophthalmologist services and general practitioner services will be collected using a patient questionnaire (Additional file 4). Costs will be calculated by combining volume of services and corresponding unit costs.

#### Patient costs

Travel costs will be calculated based on information on travel time and bringing a companion.4.*Patient satisfaction*. Previously validated patient satisfaction instruments were found too comprehensive and not suitable to assess the IVI treatment in the injection room setting. A short and simple study-specific patient satisfaction questionnaire was therefore developed in accordance with guidelines for measuring the quality of health services [16]. The questionnaire was validated for reliability and feasibility in a pilot study of 10 patients. After this first pilot test, some modifications were made to the questionnaire before a second pilot test was carried out and validated. We found the best alternative for the patients with blurred vision following treatment to be a five-point grading scale and only a few questions read out load. Only two aspects of the treatment is tested; the general impression of the treatment and the confidence during the treatment in the injection room (Additional file 5). If the patient is not giving the maximum score of satisfaction, an open-ended question will be asked for recommendations of how to improve the comfort and well-being during the visit. At the last visit, the patients additionally will be asked if they think they are treated by a nurse or by a physician.

### Data collection

At the first visit, background information for the economic evaluations is collected (Additional file 4). A physician, orthoptist or optician is asking these questions before refractioning the study eye and measuring the best corrected visual acuity. The study participant then goes to the injection room. After the IVI, the participant is asked to answer the patient satisfaction questionnaire by a secretary (Additional file 5). Each study participant has an individual study booklet marked with study number and patient initials. The booklet follows the patient during the visit in the department and is otherwise kept in a locked room.

In the following visits the study participant will be asked follow-up questions regarding use of health care service (Additional file 4). The questions are asked by the nurse or physician performing the IVI.

The last visit of the 12 month period is performed similar to the baseline registration (Additional file 4). The time window for the final test is 12 ± 2 months.

The nurse or physician performing the IVI, will fill in a daily report including the number of patients and eyes treated and number of questions asked a senior consultant (Additional file 3).

Researchers will continually examine the study forms in the booklets for missing data. Missing data will be sought collected via phone calls.

### Statistical methods

The primary objective will be analyzed using a t-test for non-inferiority, comparing mean change in visual acuity from baseline to 12 months between nurses and physicians. A linear regression model for the change in visual acuity will be used to compare the treatments after adjusting for diagnosis, used as a stratification variable. Adjusting for the other stratification variable, first or follow up treatment, can be done similarly, but will depend on a sufficient number of included patients in each of the two groups. The data will be analyzed and presented according to the CONSORT guidelines for reporting noninferiority trials [17].

Costs will be examined by analyzing differences between nurses and physicians in total cost per patient, health service cost per patient and hospital cost per patient. Imputation will be used on missing data. Sensitivity analyses will be performed to assess parameter uncertainty.

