### Randomization and blinding

Patients are randomly assigned to receive treatment by nurse or physician in a 1:1 ratio, using a web-based algorithm. The randomization is stratified by diagnosis (AMD, RVO and DME) and by number of treatments (first treatment vs treated before). The reason for choice of stratification is that there is an expected difference in change in mean visual acuity during the observation period in these groups. Only one eye per patient is included in the study. If both eyes are eligible, the eye with the better visual acuity is included.

The study is single-blinded, i.e. patients are blinded to intervention group. Patients are not told to which group they have been randomized, and both nurses and physicians will wear white hospital clothes but no nametags telling their profession during the procedure. Furthermore, when the patient enters the injection room the personnel will present themselves by first name only.

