#### Sample size considerations

In contrast to earlier studies comparing the effect of two different anti-VEGF drugs or the effect of different anti-VEGF treatment strategies, we want to test the effect of two different professions performing the treatment. Historical data from large randomized clinical AMD trials found the mean change in visual acuity during the first year of treatment to be 6–7 letters (1,2–1,4 lines) [18]. The CATT study was as the present study designed as a noninferiority study. As the noninferiority margin (δ_L_) should be less than the observed change in visual acuity, five letters (one line on the visual acuity chart) was chosen as the acceptable difference for the tested treatment to be considered noninferior to the reference treatment. However, in a study of the safety of nurse-administered IVI, a noninferiority margin of five letters may be considered too wide.

First the study population in the present study is not as homogenous as the before mentioned study since it includes both patients with AMD, RVO and DME. There is an anticipated difference in treatment response in these three conditions. Second, the majority of study participants will already have received several IVI before inclusion in the study and in these patients we do not expect major changes in visual acuity during the study period. Third, we should consider the ethical aspect of having a wide noninferiority margin; if it is right to sacrifice visual acuity to gain the possible benefit of cost savings by nurses treating the patients. Taking these aspects into consideration, we find that the noninferiority margin should not exceed three letters. In other words, the present study will test whether IVI administered by nurses is not less effective than treatment by physicians, by more than three letters.

We assume that the standard deviation (SD) of the distribution of changes, σ, will be 10 letters. This is again less than in the studies forming the basis for IVI of anti-VEGF, finding a SD of 15 letters reasonable the first year. The second year, however, the standard deviation, dropped to 11 letters and in our study we do assume 10 letters would be reasonable [8].

The anticipated true difference between the treatment groups is 0. That is, the effect of the treatment is expected to be equal in the two groups.

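### The deciding noninferiority test is an unadjusted t-test on change that leaves out baseline acuity and the randomisation strata, giving up a modest amount of precision at no saving

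*Protocol article*

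**What the plan says.** In the protocol article, Statistical methods assigns the primary objective to one test: "The primary objective will be analyzed using a t-test for non-inferiority, comparing mean change in visual acuity from baseline to 12 months". No covariate is named for it.

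The same paragraph then adds a model: "A linear regression model for the change in visual acuity will be used to compare the treatments after adjusting for diagnosis". On treatment history it says: "Adjusting for the other stratification variable, first or follow up treatment, can be done similarly", on condition that both groups hold enough patients. The text does not say how this regression bears on the margin.

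Randomization and blinding explains that diagnosis and treatment history were made strata because "there is an expected difference in change in mean visual acuity during the observation period in these groups".

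Data collection places the first-visit questions "before refractioning the study eye and measuring the best corrected visual acuity", and the injection comes afterwards. Baseline acuity is therefore recorded before treatment, and it is needed in any case to form the change score.

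On the margin, Sample size considerations says "we find that the noninferiority margin should not exceed three letters". On the spread it says "We assume that the standard deviation (SD) of the distribution of changes, σ, will be 10 letters", while reporting for earlier trials "finding a SD of 15 letters reasonable the first year" and 11 letters in the second year.

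**The concern.** Change in acuity usually depends on the starting value, through ceiling effects and regression to the mean. If it does so here, a t-test on change leaves explainable variation in the standard error. The strata raise the same issue. The design balances the arms on two factors because they are expected to predict change, and the deciding test then ignores both. If that balance is achieved, the test's standard error still contains between-stratum variation that the design has removed from the comparison.

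The cost is an interval wider than the collected data require, judged against a margin of only three letters. There is little slack: planned power is about 80%, the assumed SD is below both figures cited from earlier trials, and Trial status says recruitment has ended. More precision can now come only from the analysis.

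**Working it through.** **Inputs from the article.** Margin 3 letters, SD of change 10, true difference 0, significance level 0.05, power 80%, 140 completers per arm.

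**Reproducing the plan's figure.** With a one-sided 5% level, n = 2(1.645 + 0.842)² × 10² / 3² gives 138 per arm. The noncentral-t version gives 139, and power at 140 is 80.5%. The stated 140 is therefore reproduced for the unadjusted comparison. At one-sided 2.5% the need would be 175–176 per arm, so the plan was evidently sized at one-sided 5%.

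**Unadjusted precision.** SE = 10 × √(2/140) = 1.195 letters. The 90% confidence interval half-width is 1.645 × 1.195 = 1.97 letters.

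**Baseline-adjusted precision.** Let ρ be the correlation between baseline and 12-month acuity, with equal variances at both visits. The variance is then multiplied by (1 + ρ)/2 and the residual SD is 10 × √((1 + ρ)/2). The article does not give ρ, so 0.6 to 0.9 is an assumption. The power columns are noncentral-t at 140 per arm.

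| ρ (assumed) | Variance saved | Residual SD | 90% half-width | Power, one-sided 5% | Power, one-sided 2.5% |
|---|---|---|---|---|---|
| none (t-test) | – | 10.00 | 1.97 | 80.5% | 70.6% |
| 0.9 | 5% | 9.75 | 1.92 | 82.2% | 72.8% |
| 0.8 | 10% | 9.49 | 1.87 | 84.0% | 75.1% |
| 0.6 | 20% | 8.94 | 1.76 | 87.6% | 79.9% |

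**Which end of the range is plausible.** Under the same model, an SD of change of 10 implies a between-patient SD of acuity of 10/√(2(1 − ρ)). That is about 11 letters at ρ = 0.6, 16 at 0.8 and 22 at 0.9. Trial recruitment sets no acuity limits and admits three diagnoses, both new and already treated. A spread of only 11 letters would be narrow for such a population. Most participants are also expected to be already treated, with little change. Both points favour high ρ and the smaller gains.

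**Chance imbalance.** A baseline difference D between arms moves the change-score estimate by (1 − ρ)D in size. For an assumed D of 2 letters this is 0.8 letters at ρ = 0.6 and 0.2 at ρ = 0.9. Adjustment removes this part.

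**The strata.** Take an assumed 10% to 30% of patients at first treatment. For them, use the 6–7 letter first-year gain that the article cites from AMD trials; for the rest, assume no mean change. The between-group variance is q(1 − q)d²: from 0.1 × 0.9 × 6² = 3.2 to 0.3 × 0.7 × 7² = 10.3, that is 3% to 10% of a total of 100. This gain may overlap with that from baseline, so the two should not be added.

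**If the SD is larger than planned.** At SD 11 the unadjusted power is 73.6%. Baseline adjustment brings it to 77.5% (ρ = 0.8) or 81.6% (ρ = 0.6).

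**The case against.** The best defence is that nothing here is wrong. The hypotheses, the test and the sample size all concern unadjusted mean change, the t-test keeps its error rate, and 140 per arm delivers the stated power. The gain rests on a correlation the article does not give, and at ρ of 0.8 to 0.9 it is 0.05 to 0.10 letters of half-width. Covariates are also often settled in an analysis plan that is not shown. Most of this stands, and it limits the size of the point. The last argument does not remove it, because the article itself fixes the primary test and names the regression's covariates.

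Three stronger readings are tempting and are not supported.

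- A reader might infer that two analyses compete and nothing says which decides. Statistical methods assigns the primary objective to the t-test, so if the two disagree, the t-test governs.
- A reader might infer that a baseline imbalance passes in full into the estimate. Only the share 1 − ρ does, and it is random error already counted in the t-test's standard error, not bias. At ρ = 0.6, for example, the SE of the baseline difference is 11.18 × √(2/140) = 1.34, and 0.4 × 1.34 = 0.53. Adding this to the adjusted SE of 1.07 in squares gives 0.53² + 1.07² = 1.43 = 1.195².
- A reader might infer that the regression covers diagnosis alone. It also provides, conditionally, for treatment history.

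**Conclusion.** The point holds as a recommendation on efficiency. The deciding test uses neither baseline letters nor the strata, and baseline letters appear in no stated model. For ρ of 0.6 to 0.9 the t-test's half-width is 0.21 to 0.05 letters larger than necessary, and its power is about 7 to 2 percentage points lower, with the smaller figures more likely. These sizes rest on equal variances at the two visits, an SD of change of 10, 140 completers per arm and the assumed ρ. There is no gain from baseline only if the slope of 12-month on baseline acuity is exactly 1. The gain is worth more if the SD proves larger than planned or if the test is run at one-sided 2.5%. The validity of the t-test and its stated power are not in question.

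**What to change.** Name one deciding analysis: a linear model for 12-month acuity (or, equivalently for the arm effect, for change) with arm, baseline letters, diagnosis and first versus follow-up treatment. Declare noninferiority if the lower confidence limit of the adjusted nurse minus physician difference exceeds −3. State in advance how a sparse treatment-history stratum will be pooled, so that the covariate set does not depend on results. Keep the unadjusted t-test as a supportive analysis.

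The cost is a sentence or two, fixed before outcomes are examined by arm; the article has data collection running to January 2017. No new data are needed and the treatment difference being estimated stays the same. The model uses four more degrees of freedom than the t-test (one for baseline, two for diagnosis, one for treatment history), leaving 278 − 4 = 274.

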## Discussion

The primary objective of the study is to evaluate safety of nurse-administered IVI of anti-VEGF compared with physician-administered IVI. Anti-VEGF IVI represents a considerable workload on ophthalmologic clinics and will probably continue to do so in the near future. Extending the roles of other health workers may relieve this workload from ophthalmologists and several clinics have had good experience training nurses to perform IVIs independently [11–14]. However, none have as far as we know, investigated the safety, cost and patient acceptance of independent IVI administration by trained nurses in a RCT.

We have chosen visual acuity as the primary outcome of the present study. The major goal is to investigate safety of nurse-administered IVI and visual acuity is recommended by health authorities in clinical trials when investigating this outcome [19]. Furthermore, most patients probably want to be sure that nurse-administered IVI does not pose any increased risk of deteriorating their sight.

It is conceivable that several aspects of the IVI procedure may affect visual acuity: the injection technique may be unsatisfactory performed so that the drug may not be administered correctly into the tissue where it acts, contraindications may be misinterpreted putting the patient at risk of complications or the treatment plan may be misinterpreted so that patients receive IVI with too lengthy intervals. The training and certification of the nurses is a key in this context, and the present study is in many ways a test of whether the training of nurses was adequate or not.

We believe that the design of the study, the randomization procedure and outcome measurements will be of sufficient strength and quality to evaluate if nurses are performing IVIs as safe as the standard care. Both newly remitted patients and patients treated before are invited to participate in the study and our experience so far is that it is easier including patients familiar with the treatment than the newly remitted patients. If few newly diagnosed patients are included, the interpretation of results will be for the follow-up patients only.

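### The primary t-test ignores both randomisation strata, and adjustment for prior treatment hangs on an undefined count that a one-degree-of-freedom term does not need

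*Protocol article*

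**What the plan says.** All references are to the protocol article.

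- **Randomization and blinding.** "The randomization is stratified by diagnosis (AMD, RVO and DME) and by number of treatments (first treatment vs treated before"). The reason given is that "there is an expected difference in change in mean visual acuity during the observation period in these groups".
- **Sample size considerations.** Large AMD trials showed a mean change of 6 to 7 letters in the first year of treatment. Most participants here will already have had several injections, and "in these patients we do not expect major changes in visual acuity during the study period".
- **Statistical methods, first analysis.** "The primary objective will be analyzed using a t-test for non-inferiority, comparing mean change in visual acuity from baseline to 12 months". This sentence carries no condition and names no covariate.
- **Statistical methods, second analysis.** "A linear regression model for the change in visual acuity will be used to compare the treatments after adjusting for diagnosis".
- **Statistical methods, third analysis.** Adjustment for first or follow-up treatment "can be done similarly, but will depend on a sufficient number of included patients in each of the two groups". No number, decision time or ranking of the analyses follows. The two groups could be the two strata or the two arms.
- **Discussion.** "If few newly diagnosed patients are included, the interpretation of results will be for the follow-up patients only". No threshold is given here either.

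**The concern.** The design section treats prior treatment as prognostic enough to stratify on. The analysis section then leaves it out of the primary test and makes it optional in the regression. Diagnosis is the same kind of factor and has more levels, yet it is adjusted for without any condition.

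Two things are at stake.

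1. **Precision.** Stratified allocation removes between-stratum variation from the arm comparison. A t-test that ignores the strata leaves that variation in its standard error, so the interval is wider than it need be and noninferiority is harder to show.
2. **Clarity about the deciding result.** Up to three comparisons with the 3-letter margin can coexist: unadjusted, adjusted for diagnosis, and adjusted for both factors. The t-test is attached to the primary objective, but the text does not say what follows if a regression disagrees with it, or whether the third analysis will exist at all.

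**Working it through.** **Inputs from the article:** margin 3 letters, SD 10 letters, true difference 0, significance level 0.05 (sidedness not stated), power 80%, 140 completers per arm, 8% dropout, 152 randomised per arm, first-year change 6 to 7 letters in AMD.

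**Assumptions (not in the article):** a difference d = 6.5 letters in mean change between first-treatment and previously treated patients (midpoint of 6 to 7, set against zero), and a first-treatment share p of 5 to 20%. The article says only that previously treated patients are the majority.

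**Step 1. Reproduce the sample size.** n per arm = 2(z₁₋α + z₁₋β)²σ²/δ² = 2 × (1.645 + 0.842)² × 100/9 ≈ 137.4, so 138. This agrees with 140 to within two patients. One-sided 0.025 gives 175, so the stated 0.05 is one-sided. For dropout, 140/0.92 = 152.2, against 152 in the article. Normal-approximation power at 140 per arm is 80.7%.

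**Step 2. Cost of the covariate.** The t-test has 280 − 2 = 278 residual degrees of freedom. One two-level main effect leaves 277. Adding diagnosis (two more) leaves 275. None of this depends on how many patients are in the smaller stratum. Small counts would limit a stratum-specific estimate or an interaction, which is not what the sentence describes.

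**Step 3. Variance carried by the factor.** Between-stratum variance = p(1 − p)d², with d² = 42.25. Residual SD = √(100 − p(1 − p)d²).

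| Share p | p(1 − p)d² | % of 100 | × 280 patients | Residual SD | n per arm | Power at 140 |
|---|---|---|---|---|---|---|
| 5% | 2.01 | 2.0% | 5.6 | 9.90 | 135 | 81.3% |
| 10% | 3.80 | 3.8% | 10.6 | 9.81 | 133 | 82.0% |
| 20% | 6.76 | 6.8% | 18.9 | 9.66 | 129 | 83.0% |

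The comparison values without adjustment are 138 per arm and 80.7%. If d ranges from 3 to 10 letters over the same shares, power with adjustment ranges from 80.8% to 86.3%.

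**Step 4. Does the choice of analysis change the verdict?** A simulation compared the unadjusted t-test with a model adjusted for prior treatment only. It used 40,000 runs per setting, 140 per arm, one-sided 0.05, total SD 10, and strata balanced between arms to within two patients.

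| Setting | Type I error, unadjusted | Adjusted | Whichever passes | Verdicts differ at true difference 0 |
|---|---|---|---|---|
| p = 10%, d = 6.5 | 0.048 | 0.052 | 0.054 | 1.7% |
| p = 10%, d = 10 | 0.042 | 0.049 | 0.051 | 2.8% |
| p = 30%, d = 6.5 | 0.041 | 0.048 | 0.049 | 2.3% |
| p = 30%, d = 10 | 0.034 | 0.050 | 0.050 | 5.0% |

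The unadjusted test falls below its nominal level, and taking whichever analysis passes stays close to 0.05. Without any balance on the stratum, taking whichever passes would give 0.056 to 0.068, but the article's stratified randomisation makes that an upper bound rather than the expected case.

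**The case against.** The strongest reply has four parts.

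- **A primary analysis is named.** The t-test is tied to the primary objective without condition. A reader might infer that the analysts may freely choose between two noninferiority results after seeing the data. The text does not support that: the condition turns on how many patients are enrolled, not on outcomes, and the Trial status section says recruitment ended in December 2015 while data collection runs to January 2017. What stands is that no threshold or decision time is written down, and the regressions are not ranked against the t-test.
- **The effect is small and in the safe direction.** This stands. An interval that is too wide works against a noninferiority claim. A reader might compute a larger figure from an even split: 0.5 × 0.5 × 42.25 = 10.6, or about 30 of 280 patients. That does not apply, because at 50% both groups are large, so the count condition would be met on any reasonable reading. The article also expects most patients to be already treated.
- **The Discussion sentence is not an analysis switch.** A reader might infer that it changes the population analysed. It concerns interpretation and alters no analysis set, test or margin. Only its undefined trigger is open to criticism.
- **Covariate lists and thresholds belong in an analysis plan.** That is fair for missing detail. Here, however, the article states a condition, and the condition has no technical basis.

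**Conclusion.** The point holds as a modest, correctable weakness in the analysis. The article stratifies on two factors it expects to matter, assigns the primary objective to a test that uses neither, and makes adjustment for one of them depend on an undefined count that is not needed.

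The loss is about 2 to 7% of the planning variance, or roughly 6 to 19 of 280 patients and 0.6 to 2.3 percentage points of power at 140 per arm. This rests on the assumed 6.5-letter difference, which comes from first-year AMD results applied to a mixed AMD, RVO and DME population, and on an assumed first-treatment share of 5 to 20%.

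The figures do not support a claim of materially inflated type I error. Among the simulated settings with near-balanced strata, the highest value from taking whichever analysis passes was 0.054.

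**What to change.** 1. Delete the condition on stratum counts.
2. Name one linear model for change in visual acuity, with arm, diagnosis (three levels) and prior treatment (two levels), as the analysis that decides noninferiority against the 3-letter margin, whatever the stratum counts. In a linear model with main effects, the arm coefficient remains a difference in mean change in letters, so the margin carries over unchanged.
3. Keep the unadjusted t-test as a supporting analysis that does not decide the conclusion.
4. State the primary conclusion for all randomised patients. Show the arm difference and 95% CI separately for first-treatment and previously treated patients as description, so that the Discussion caveat concerns generalisation only.

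**Cost.** This replaces the named primary test, so it should be recorded openly as a change of primary analysis, dated before final outcomes are complete. It needs no new patients or data, since both factors are recorded at randomisation, and it uses three further degrees of freedom.
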